### Recruitment

Individuals matching the inclusion criteria for the Fex-Can RCT will be sent an information letter outlining the study procedures and the voluntary nature of participation. Based on the self-reported problems at the baseline assessment of the Fex-Can Cohort, potential participants will be invited to participate in the RCT, for either the Fex-Can Sex or the Fex-Can Fertility. Acceptance of participation in the RCT is provided by return of a written informed consent form. Two reminders will be sent to non-responders. Based on some difficulties recruiting participants to the feasibility study of the Fex-Can [24] the information letter states that participants will receive two cinema tickets (total value of approximately 20 Euro) as incentives for completion of each assessment. No incentive will be offered for participation in the post-intervention semi-structured interview.

### Randomization

Participants will be randomly assigned to either intervention or control group with an allocation ratio of 1:1, allocating participants in blocks stratified by sex and diagnosis. This process will be performed separately for the arms of the RCT (Fex-Can Sex and Fex-Can Fertility). A computer-generated randomization sequence will be created by a statistician with no clinical involvement in the trial. The details of the series of random numbers is unknown to the investigators. Following randomization, participants in the intervention groups will receive a text message and/or e-mail with log-in details to the program; individuals in the control groups will be informed about their group allocation via mail or e-mail.

### Blinding (masking)

Due to the nature of the intervention, blinding of participants to researchers involved in providing and monitoring the intervention and data collection is not possible. However, participants’ allocation to intervention or control groups will be masked in the data set available for researchers during data analysis.

### Statistical methods

Besides descriptive statistics and visualizations, the main class of statistical method used will be linear mixed models for longitudinal data. The statistical analyses will primarily focus on comparing the Fex-Can intervention with standard care between baseline and directly after end of program. Missing data will be analyzed using descriptive statistics and significance testing. Intention-to-treat will be applied for analyses of the primary outcomes. Statistical analyses will be performed in collaboration with external statisticians, who are not informed about the study participants’ group allocation. SPSS Statistics version 25 (IBM Corp., Armonk, N.Y., USA) will be the primary tool for data management and statistical analyses.

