**Methods:**

The trial has an randomized clinical trial (RCT) design with two parallel arms. The active groups receive either the version of the Fex-Can intervention targeting sexual problems or the version targeting fertility-related distress. Control groups receive standard care. Primary outcomes will be sexual function assessed with the Patient-Reported Outcomes Measurement Information System® Sexual Function and Satisfaction measure version 2.0 (SexFS) and fertility-related distress assessed with the Reproductive Concerns After Cancer scale (RCAC). The effect of the intervention will be evaluated directly after end of the program. Primary and secondary outcomes will also be assessed at the short- (12 weeks after end of program) and long-term (20 and 44 months after end of program) follow-up. At least 64 completers will be needed in each arm (total *n* = 256) to achieve adequate statistical power in the analyses. In order to increase the understanding of how the intervention brings about a possible change, semi-structured interviews will additionally be conducted with a purposeful sample shortly after completion of the intervention.

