### Sample size

To detect a statistically significant difference with a power of 80%, estimating medium effect size (0.5) and α = 0.05, a total of 128 completers (post-intervention assessment) will be needed in the Fert-Can Sex and Fex-Can Fertility, respectively. We expect approximately 80% (*n* = 840) of the estimated 1050 participants in the Fex-Can Cohort to rate sexual dysfunction and/or a high level of fertility distress. Of these we expect approximately 50% (*n* = 420) to agree to participation in the RCT, i.e. 210 participants in the Fex-Can Sex and the Fex-Can Fertility, respectively. We estimate an attrition of 15% at the post-intervention assessment (directly after end of program) and another 15% at the short-term follow-up (12 weeks after end of program), leaving 151 participants in the Fex-Can Sex and Fex-Can Fertility, respectively. We therefore estimate that the planned number of approached individuals will be sufficient to achieve adequate statistical power.

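### The primary comparison is worded as baseline-to-post change without the randomisation strata; a baseline-adjusted model with sex and diagnosis would use the same data more efficiently

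*Protocol article*

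**What the plan says.** Three sections of the protocol article bear on this.

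- **Statistical methods** names linear mixed models as the main method and describes the primary focus as: "The statistical analyses will primarily focus on comparing the Fex-Can intervention with standard care between baseline and directly after end of program". It does not say how baseline enters the model, and it lists no covariates.
- **Sample size** works from 80% power, "estimating medium effect size (0.5) and α = 0.05", and concludes that "a total of 128 completers (post-intervention assessment) will be needed" for each of the two programmes. The Abstract gives the same figure per randomised group: "At least 64 completers will be needed in each arm". Neither place says which SD the 0.5 refers to, and no baseline-post correlation is given.
- **Randomization** describes 1:1 allocation, "allocating participants in blocks stratified by sex and diagnosis", done separately for each programme.

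The Trial design section calls the design pre-post with follow-up, and the Objectives speak of a reduction in problems. Both support reading the primary comparison as one of change.

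**The concern.** A longitudinal mixed model that leaves the baseline means free in both groups and tests group-by-time estimates the difference in mean change. With two visits and complete data this is the change-score comparison. Such a contrast carries the noise of both measurements. The sample size carries no correlation term and matches a plain comparison of two means, so the article does not show that the planned number and the planned contrast were matched.

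Two things are at stake. First, precision may be given away: randomisation makes the expected baseline means equal, and a model that uses this fact is never less efficient than the change contrast, apart from one degree of freedom. Second, the randomisation is balanced within sex and diagnosis, yet the analysis as described does not carry these factors forward.

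**Working it through.** **Inputs.** Effect size 0.5, alpha 0.05, power 80% and 128 completers per programme (Sample size); 1:1 allocation (Randomization); 210 randomised per programme and 15% attrition at the post-programme assessment (Sample size). The baseline-post correlation, rho, is not in the document. It is an assumption, shown from 0.2 to 0.7.

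**Step 1: the plan's own figure.** A two-sided two-sample t-test at d = 0.5 has exact power 79.5% with 63 per group and 80.1% with 64. So 64 per group, 128 per programme, reproduces. A one-sided test would need 50 per group and does not.

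**Step 2: effective effect sizes.** Take 0.5 in SDs of the score, with the same SD at both visits.

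- Unadjusted change: variance 2(1 − rho), so d = 0.5/√(2(1 − rho)).
- Baseline-adjusted: residual variance 1 − rho², so d = 0.5/√(1 − rho²).

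At rho = 0.3 these are 0.5/√1.4 = 0.423 and 0.5/√0.91 = 0.524.

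**Step 3: power.** Expected completers are 210 × 0.85 = 178.5 per programme, about 89 per group.

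| rho | Change, 64 per group | Adjusted, 64 per group | Change, 89 per group | Adjusted, 89 per group |
|---|---|---|---|---|
| 0.2 | 60.2% | 81.7% | 74.6% | 92.3% |
| 0.3 | 66.0% | 83.7% | 80.1% | 93.5% |
| 0.4 | 72.7% | 86.5% | 85.7% | 95.1% |
| 0.5 | 80.1% | 90.0% | 91.3% | 96.9% |
| 0.6 | 88.1% | 93.9% | 96.0% | 98.6% |
| 0.7 | 95.2% | 97.6% | 99.0% | 99.6% |

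A simulation of 20,000 trials at 64 per group agreed: 66.0%, 80.7% and 95.0% for change, and 82.8%, 89.7% and 97.3% with adjustment, at rho 0.3, 0.5 and 0.7.

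**Step 4: does the ranking depend on the scale or on equal variances?** The ratio of the two variances is 2(1 − rho)/(1 − rho²) = 2/(1 + rho). This exceeds 1 for every rho below 1, whichever SD defines the 0.5. If the baseline SD is k times the post SD, the change variance is 1 + k² − 2·rho·k in units of the post variance. Subtracting 1 − rho² leaves (k − rho)², which is never negative. Adjustment is therefore never the less precise choice, apart from one degree of freedom.

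**Step 5: cost of the strata terms.** Six diagnoses and sex as main effects use 5 + 1 = 6 degrees of freedom; a full cross would use at most 6 × 2 − 1 = 11. If none of these terms predicted the outcome, power at 64 per group without baseline adjustment would go from 80.15% to 80.12% with 6 and to 80.09% with 11. The loss is under 0.1 percentage point.

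**The case against.** The strongest reply is that the Statistical methods section fixes only a model class and a time window. A mixed model with a common baseline mean, or with baseline as covariate, fits the same words. Its parameterisation and covariates are what a condensed article leaves to an analysis plan, which is not shown here. This stands in so far as no adjusted model is excluded and no error is demonstrated. It does not remove the value of stating the better model, because the wording used points the other way.

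Stronger readings are tempting, and the document does not support them.

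- A reader might infer that 80% power is reached only if rho is at least 0.5. That holds at the minimum of 64 per group, for an unadjusted change contrast, with 0.5 in score SDs and equal variances (exact threshold 0.498). If 0.5 is in SDs of the change score, power is 80.1% whatever rho is. At the expected 89 per group the threshold falls to about 0.30.
- A reader might argue that selecting participants on baseline cut-offs lowers rho and so harms the change contrast. Direct selection on baseline leaves a linear slope of post on baseline unchanged, and the change contrast loses to the post score only when that slope is below 0.5. With SD ratio k the break-even is rho = k/2, which falls when baseline is narrowed. Eligibility also rests on any one of several domains or dimensions, not on the primary score itself.
- A reader might expect a further gain in power from the strata. The document gives nothing to quantify it. Stable differences in level between strata would largely cancel in a change contrast or be absorbed by baseline adjustment. Omitting the strata would be conservative, not invalid.

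**Conclusion.** This is a free improvement, not a fault in the sample size. Read naturally, the described comparison is an unadjusted change contrast without the stratification factors. Under the score-SD reading with equal variances, baseline adjustment adds about 21 points of power at rho 0.2 (81.7 − 60.2 = 21.5), about 10 at rho 0.5 (90.0 − 80.1 = 9.9) and about 2 at rho 0.7 (97.6 − 95.2 = 2.4), all at 64 per group. At the expected 89 per group and rho 0.3 the gain is about 13 points (93.5 − 80.1 = 13.4). The size of the gain depends on rho, which is assumed; its direction does not. Because the article neither gives a correlation nor rules out an adjusted model, it cannot be said that the trial is underpowered.

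**What to change.** In Statistical methods, define the primary model separately for each programme:

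- a linear mixed model with baseline means constrained equal across groups, visit, and group-by-visit terms for the post-baseline visits (or, equivalently in purpose, the post-programme score with baseline as covariate);
- sex and diagnosis as fixed effects, matching the randomisation;
- the adjusted group difference immediately after the programme as the primary estimate.

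In Sample size, state that the 0.5 is in SDs of the post-programme score. The 64 per group can stay as it is.

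The cost is wording. Baseline scores, sex and diagnosis are already collected, no further participants are needed, and the model can be fitted in the SPSS software already named. If an unseen analysis plan already specifies such a model, one sentence saying so is enough.

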### Adverse effects

Adverse effects will be evaluated by number of participants reporting possible worsening of symptoms in the primary or secondary outcomes*.* Participants furthermore will indicate in the post-intervention survey if they have experienced worsening of symptoms of any kind. Additionally, the semi-structured post-intervention interview will include a question regarding possible adverse effects experienced by the participants.

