### Primary outcomes

#### Sexual function

The SexFS (version 2) is a set of measures developed to assess sexual function and satisfaction in both men and women, regardless of sexual orientation and if currently being sexually active with partner/s or not. The primary outcome for the Fex-Can Sex program is the score (continuous measure) in the domain ‘Satisfaction with sex life’. This domain assesses how satisfying and pleasurable current sexual activities are perceived; two selected items will be used that are scored on a five-point scale (ranging from 1 = None/Not at all to 5 = Very/A lot). Item response theory is used to calculate the domain score which is transformed to a T-score metric where 50 represents the mean for the American general population (standard deviation = 10) [21]. Sexual dysfunction is defined as 0.5 SD (5 points on the T-scale) from the population mean of 50 in the respective domain. The SexFS has shown adequate content, construct and known-groups validity as well as test-retest reliability [21, 25]. The selected items and domains of the SexFS have been translated into Swedish and linguistically validated in accordance with the procedure developed by FACITrans and PROMIS [26].

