### Process evaluation

#### Post-intervention survey

As part of the post-intervention assessment, participants in the intervention groups (Fex-Can Sex and Fex-Can Fertility) will be requested to respond to 13 study-specific items concerning their adherence, i.e. use of the different features of the intervention (e.g. texts, exercises and videos). They will also be asked to state their opinions about the content and features of the intervention. Responses are given on a four-point scale ranging from “Disagree completely” to “Agree completely”. In addition, participants will be requested to declare their current level of problems (regarding sex-life or fertility-related distress) in comparison with their level of problems before they entered the Fex-Can intervention. Responses are given on a 7-point scale, ranging from “Much improved” to “Much worsened” with the midpoint “No change”.

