#### Semi-structured interview

In order to increase the understanding of how the intervention is used by participants and how it brings about a possible change in the outcomes, semi-structured interviews will be conducted with a purposive sample of approximately 30 participants shortly after completion of the intervention. During these interviews, which will be conducted via telephone and transcribed verbatim, participants’ views of their sexual dysfunction or fertility-related distress and if/how these problems have changed during the course of the intervention will be explored. Participants will also be asked to describe their experiences of participating in the intervention and their use of the different program functions. Transcripts of the interviews will be analyzed using [qualitative] content analysis [33].

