### Participant timeline

The Fex-Can project includes a large population-based cohort study with an embedded RCT. This means that participants in the Fex-Can RCT will be identified among participants of the Fex-Can Cohort, based on their self-report of sexual function and fertility distress at the base-line assessment. Following randomization of those who accept participation in the RCT, the intervention groups (IG) receive access to the web-based intervention delivered over 12 weeks and the control groups (CG) receive standard care. All participants (IG and CG) will be requested to complete two assessments (on paper); directly after and 12 weeks after end of program. The long-term follow-up assessments (20 and 44 months after end of program) will be conducted as part of the data collection for the Fex-Can Cohort, and will be completed on paper or via the web. Primary and secondary outcomes of the Fex-Can RCT are measured pre-treatment (baseline assessment of the Fex-Can Cohort), at post-intervention assessment, and at the short- and long-term follow-up assessments. See Table 1 for study timeline.

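### The adverse-effects count states no size of worsening and no comparison with control, and the self-reports of worsening appear to have no control counterpart

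*Protocol article*

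**What the plan says.** The Adverse effects section of the protocol article names three sources of harm data.

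- **Outcome scores:** "Adverse effects will be evaluated by number of participants reporting possible worsening of symptoms in the primary or secondary outcomes".
- **A survey question:** "Participants furthermore will indicate in the post-intervention survey if they have experienced worsening of symptoms of any kind".
- **An interview question** about adverse effects.

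The section gives no size of decline, no time point and no comparison of groups.

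Two other sections show who supplies the second and third sources. Under Post-intervention survey, "participants in the intervention groups (Fex-Can Sex and Fex-Can Fertility) will be requested to respond to 13 study-specific items". The same paragraph adds a 7-point rating of current problems "in comparison with their level of problems before they entered the Fex-Can intervention". Under Semi-structured interview, the interviews are held with a "purposive sample of approximately 30 participants shortly after completion of the intervention".

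The outcome scores themselves are collected in both groups. Participant timeline says: "All participants (IG and CG) will be requested to complete two assessments (on paper); directly after and 12 weeks after end of program". It also says: "Primary and secondary outcomes of the Fex-Can RCT are measured pre-treatment (baseline assessment of the Fex-Can Cohort), at post-intervention assessment".

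**The concern.** A head count over many scores has a high background rate. Individual scores move up and down between assessments without any harm, and the more scores there are, the more people move the wrong way on at least one. Without a size of worsening and a control rate beside it, the count cannot be read as harm.

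Two design features make the control rate matter more. The Eligibility criteria select people for poor baseline scores, so regression to the mean will tend to improve the selected scores and can mask true worsening. The trial is also unblinded to participants, so self-reported worsening in one group alone is hard to interpret.

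The self-report items are the part that later analysis cannot repair. A threshold can be added in an analysis plan, but answers that controls were never asked for cannot be recovered.

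**Working it through.** The protocol gives no figure for this rule, so there is none to reproduce.

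**Step 1. Number of scores (Primary outcomes and Secondary outcomes).** Shared by both programmes: Body Image Scale 1, QLQ-C30 summary score 1, HADS 2, self-efficacy 1, total 5.

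- Fertility: RCAC 1 + knowledge 1 + 5 = 7.
- Sex, men: satisfaction 1 + common SexFS domains 4 + erectile function 1 + 5 = 11.
- Sex, women: satisfaction 1 + common SexFS domains 4 + female domains 4 + 5 = 14.

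If 'symptoms' is read to leave out knowledge and self-efficacy, these become 5, 10 and 13.

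**Step 2. Share flagged on at least one of k scores with no true change.** Let p be the chance that one score counts as worse, and ρ the correlation between changes. The protocol gives neither, so both are assumptions.

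- Independent changes: 1 − (1 − p)^k. For example, p = 0.5, k = 7: 1 − 0.5^7 = 0.992. With p = 0.1, k = 7: 1 − 0.9^7 = 0.522.
- Equally correlated normal changes: 1 − E[(1 − Φ((Φ⁻¹(p) − √ρ·Z)/√(1 − ρ)))^k], with Z standard normal.

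Results for k = 7 / 11 / 14:

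| p | ρ = 0 | ρ = 0.3 | ρ = 0.5 |
|---|---|---|---|
| 0.5 | 0.992 / 1.000 / 1.000 | 0.936 / 0.969 / 0.980 | 0.875 / 0.917 / 0.933 |
| 0.4 | 0.972 / 0.996 / 0.999 | 0.879 / 0.933 / 0.952 | 0.800 / 0.857 / 0.881 |
| 0.3 | 0.918 / 0.980 / 0.993 | 0.787 / 0.866 / 0.898 | 0.696 / 0.767 / 0.800 |
| 0.2 | 0.790 / 0.914 / 0.956 | 0.643 / 0.745 / 0.791 | 0.551 / 0.632 / 0.671 |
| 0.1 | 0.522 / 0.686 / 0.771 | 0.414 / 0.517 / 0.572 | 0.345 / 0.419 / 0.459 |

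The row p = 0.5 means that any drop counts and there are no ties. The row p = 0.4 allows for some ties. The narrower count of 5 lowers the figures but does not remove the problem: under independence it gives 1 − 0.5^5 = 0.969 at p = 0.5 and 1 − 0.9^5 = 0.410 at p = 0.1.

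**Step 3. What threshold gives a small p?** With test-retest correlation r (assumed), the SD of a change is √(2(1 − r)) score SDs, and p = Φ(−threshold/√(2(1 − r))).

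- A drop of 0.5 SD: p = 0.309, 0.259 and 0.215 at r = 0.5, 0.7 and 0.8.
- A drop of 1 SD: p = 0.159, 0.098 and 0.057.

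A half-SD change threshold therefore still leaves p at about 0.2 to 0.3.

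**Step 4. Room left to see harm.** At p = 0.5 and ρ = 0.3, the control group would already be at 93.6% (k = 7) or 98.0% (k = 14). An excess in the intervention group could then be at most 6.4 or 2.0 percentage points, however real the harm.

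**Step 5. Which source has a control counterpart?** The outcome scores do, by Participant timeline. The 7-point rating does not: it is given to the intervention groups and refers to entering the intervention, so controls could not answer it as worded. The interview follows completion of the intervention. For the any-worsening question, Adverse effects says only participants, but places it in the post-intervention survey, whose study-specific items are described elsewhere as going to the intervention groups.

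**The case against.** Three stronger readings are tempting, and the document does not support them.

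- **That the harm rule has no control rate.** Both groups complete the primary and secondary outcomes at baseline and after the programme, so a control count of worsening can be produced. Average deterioration against control can be examined too. A reader should not conclude that safety cannot be assessed at all.
- **That the rule flags almost everyone.** This needs any drop to count, few ties and weak to moderate correlation. The sentence never says at least one score or any decline, and a table per outcome would fit its wording. Ties are likely on short scales: the primary outcome in Fex-Can Sex uses two five-point items, and several secondary domains have one.
- **That the protocol already supplies a change threshold of 5 T-score points.** That value, under Sexual function, is a distance from the population mean that defines dysfunction at one time. It is not a criterion for change within a person.

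It can also be said that a threshold and a comparison table are details an article may leave to the full protocol or analysis plan. That stands for the threshold. It does not stand for who is asked the self-report items, which is data collection described in this article. The intervention-only reading of the any-worsening question is an inference from a shared survey name, and is put here as such. The 7-point rating is certainly intervention-only, but it is described under process evaluation and Adverse effects does not name it.

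**Conclusion.** The point holds in a limited form. As described, the outcome-based count has no stated size of worsening and no stated comparison with control. Read as a pooled count, it is dominated by chance: about 80 to 100% flagged at p of 0.4 to 0.5, and about 35 to 96% at p of 0.1 to 0.2, over ρ of 0 to 0.5 and k of 7 to 14. These ranges rest on assumed p and ρ, equal correlation, normal changes and no true change. Regression to the mean would lower p for the scores used in selection.

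The control data needed to read the outcome scores properly will exist. The 7-point rating has no concurrent comparator, and the any-worsening question probably has none. This is an inexpensive improvement that should be made. It is not a flaw that invalidates the trial.

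**What to change.** 1. Report deterioration separately for each outcome, beyond a change threshold fixed before unmasking: a reliable-change value or a justified minimal change. Do not carry over the 0.5 SD dysfunction cut-off unexamined.
2. Compare the proportions between intervention and control within each programme, with confidence intervals, leading with the primary outcome and the two HADS scales. State the time point.
3. Put the any-worsening question and the 7-point change item into the post-intervention paper survey of both groups, worded without reference to the intervention, for example 'compared with three months ago'.
4. Reconcile the unqualified reference to participants under Adverse effects with the restriction to intervention groups under Post-intervention survey.

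The cost is one or two extra items for controls, a survey amendment and one added table. The appendix lists the trial as recruiting, so controls who have already passed that assessment would not be covered.

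The comparison will be imprecise. With 64 per group and deterioration of 20% against 30%, the 95% interval for the difference has a half-width of 1.96 × √((0.2 × 0.8 + 0.3 × 0.7)/64) = 0.149, and power is about 26%. That is a reason to report intervals, and not to read a non-significant test as evidence of safety.
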